## Abstract

**Background:**

Caesarean section (CS) rates are rising worldwide. In the Netherlands, the most significant rise is observed in healthy women with a singleton in vertex position between 37 and 42 weeks gestation, whereas it is doubtful whether an improved outcome for the mother or her child was obtained. It can be hypothesized that evidence-based guidelines on CS are not implemented sufficiently.

Therefore, the present study has the following objectives: to develop quality indicators on the decision to perform a CS based on key recommendations from national and international guidelines; to use the quality indicators in order to gain insight into actual adherence of Dutch gynaecologists to guideline recommendations on the performance of a CS; to explore barriers and facilitators that have a direct effect on guideline application regarding CS; and to develop, execute, and evaluate a strategy in order to reduce the CS incidence for a similar neonatal outcome (based on the information gathered in the second and third objectives).

**Methods:**

An independent expert panel of Dutch gynaecologists and midwives will develop a set of quality indicators on the decision to perform a CS. These indicators will be used to measure current care in 20 hospitals with a population of 1,000 women who delivered by CS, and a random selection of 1,000 women who delivered vaginally in the same period. Furthermore, by interviewing healthcare professionals and patients, the barriers and facilitators that may influence the decision to perform a CS will be measured. Based on the results, a tailor-made implementation strategy will be developed and tested in a controlled before-and-after study in 12 hospitals (six intervention, six control hospitals) with regard to effectiveness, experiences, and costs.

**Discussion:**

This study will offer insight into the current CS care and into the hindering and facilitating factors influencing obstetrical policy on CS. Furthermore, it will allow definition of patient categories or situations in which a tailor-made implementation strategy will most likely be meaningful and cost effective, without negatively affecting the outcome for mother and child.

**Trial registration:**

http://www.clinicaltrials.gov: NCT01261676

## Background

The worldwide rise in caesarean section (CS) rate is a major healthcare issue, with rates reported as high as 32% in the United States (US) and 37% in Brazil [1,2]. In the Netherlands, the overall CS rate has increased from 8.1% to 13.6% over the recent decade. Although this rise is relatively low compared to other countries, a striking detail is that the most impressive rise, in absolute numbers, was among healthy women with a singleton in vertex position between 37 and 42 weeks gestation [3]. However, an increasing CS rate does not imply an improved outcome for mother and infant [4]. CS are associated with an increased risk of maternal mortality as well as serious morbidity, such as admission to the intensive care unit (Odds Ratios (ORs) between 30.8 and 63.4), hysterectomy (ORs between 3.2 and 13.5), and puerperal infection (OR 3.0) [5-7].

Besides the short-term risks, CS have an impact on the mother’s future reproductive health, for example uterine rupture, placenta praevia, or placenta accreta [8,9].

There is no evidence suggesting a better neonatal outcome from the increased CS rate in terms of mortality, intracranial haemorrhage, or impaired neurological development in the general population [10,11]. In fact, an elective CS performed before 39 completed weeks is associated with respiratory distress and admission to the neonatal intensive care unit [11,12].

The question arises what causes the worldwide increase in CS rate considering the fact that in most situations there are no apparent benefits of a CS for mother and child; the costs are higher compared to vaginal birth [5]; and the incidence of both maternal and neonatal complications are increased. There are concerns about the increasing rate of planned CS as well as a declining rate of vaginal birth after a previous CS (VBAC) in the US and Australia [13,14].

To optimize CS practice, the Royal College of Obstetricians and Gynaecologists (RCOG) developed an evidence-based guideline (NICE: National Institute of Clinical Evidence) with clear recommendations for obstetric care. Similar recommendations, which have a direct effect on the decision to perform a CS, are also mentioned in the different guidelines of the Dutch Society of Obstetrics and Gynaecology (NVOG), Society of Obstetricians and Gynaecologists of Canada (SOGC), American College of Obstetrics and Gynaecology (ACOG), and National Guideline Clearinghouse from the US department of health and human services (NGC).

Despite the introduction of evidence-based guidelines, the CS rate continues to increase. We hypothesize that poor adherence to the guidelines plays a key role in the rising CS rate. In order to optimize adherence to the CS guidelines, the stepwise model by Grol can be used to select the proper strategies [15,16]. The first step in this model is to analyze the current care (measured by valid quality indicators) compared to the optimal care as described in evidence-based guidelines, and to determine which barriers and facilitators might influence the implementation of optimal care. Subsequently, a tailor-made implementation strategy can be developed with activities applied to the determined barriers. In the last step, the strategy is executed and evaluated in terms of effectiveness, feasibility, and costs*.*

In view of the rising CS rate, this study aims are:

1. To develop a set of quality indicators on the decision to perform a CS based on key recommendations of both Dutch and international guidelines.

2. To gain insight into actual adherence of Dutch gynaecologists to guideline recommendations on the performance of CS.

3. To explore barriers and facilitators that have a direct effect on application of guideline recommendations regarding CS.

4. To develop, execute and evaluate a strategy in order to improve care and possibly decrease the CS incidence for a similar neonatal outcome, based on the information gathered in steps two and three.

## Methods

The four aims were approached in four parts: the development of quality indicators, the assessment of current care, the identification of barriers and facilitators, and the development of a tailored implementation strategy and executing and evaluating this strategy in a clustered controlled before-and-after study (CBA).

### The development of quality indicators

#### Design and methods

In order to measure current Dutch practice on CS, quality indicators regarding the process, structure, and outcome of care need to be developed. This will be achieved according to the RAND-modified Delphi method [17,18]. The indicators will be based on key recommendations extracted from the guidelines of several international obstetric organisations (RCOG, NVOG, SOGC, ACOG and NGC*)*. These key recommendations will be evaluated in two rounds by an independent expert panel consisting of Dutch obstetricians and midwives. In the first round, a questionnaire will be developed on three subjects (planned CS, emergency CS, and methods to reduce the CS rate). The questionnaire will be sent to the experts who will be asked to individually rate the key recommendations on a 9-point Likert scale ranging from 1 to 9 (‘not relevant’ to ‘extremely relevant’ for measuring the quality of CS care). Furthermore, a ranking of the key recommendations will be asked per subject to ultimately extract those indicators considered to be most important for quality-of-care measurement. The experts also have the opportunity to add comments or suggest additional recommendations they consider suitable as a quality indicator. The returned questionnaires will be analysed based on the ratings of the recommendations on the 9-point Likert scale, and the median score of these items will be calculated and rated as described previously by Campbell [19]. Furthermore, scoring variables reflecting the ranking of the items in each of the three subjects will be developed (*e.g.*, in a top 3 ranking, a first ranking creates 3 points, a second ranking 2 points, and a third ranking 1 point).

The second round consists of a consensus meeting where the experts will receive their individual as well as the overall results of the first round to promote discussion. The aim of this meeting is to reach consensus on those recommendations that are most suitable for assessing the quality of care on performing CS. After consensus is reached, the recommendations will be operationalized into a set of measurable quality indicators.

### Study population and setting

A representative, national expert panel consisting of obstetricians and midwives (about 12 to 15 experts) will be invited. The obstetricians and midwives will have worked at various types of hospitals, ranging from small regional hospitals to university hospitals.

### Outcome measures

The outcome of the first step of the study is a set of valid quality indicators regarding the decision to perform a CS which can then be used to measure the current practice.

### The assessment of current care

#### Design and methods

A retrospective medical record search based on the set of quality indicators will be performed in order to assess the Dutch gynaecologists’ adherence to the CS guideline recommendations. Adherence to these indicators will be quantified, as well as the variation in care and adherence between the participating hospitals. To gain insight into the current Dutch care compared to international care, the CS percentages of the different risk groups will be calculated according to the Robson classification (Table 1) [20]. Furthermore, the maternal mortality or severe acute morbidity (Table 2) [21], and perinatal mortality or serious morbidity (pH <7.00, Apgar 5 min <7, and NICU admission) will be noted. This study will provide us with information about current practice on CS in the Netherlands and insight into the effects on outcome of mother and child.

**Table 1 T1:** Ten-group classification according to Robson

**Groups:**	
1.	Nulliparous, single cephalic, >37 weeks, in spontaneous labour
2.	Nulliparous, single cephalic, >37 weeks, induced or CS before labour
3.	Multiparous (excluding previous CS), single cephalic, >37 weeks, in spontaneous labour
4.	Multiparous (excluding previous CS), single cephalic, >37 weeks, induced or CS before labour
5.	Previous CS, single cephalic, >37 weeks
6.	All nulliparous breeches
7.	All multiparous breeches (including previous CS)
8.	All multiple pregnancies (including previous CS)
9.	All abnormal lies (including previous CS)
10.	All single cephalic, < 36 weeks, (including previous CS)

**Table 2 T2:** Inclusion criteria for severe acute maternal morbidity

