## Discussion

The CS rate in The Netherlands is comparatively low compared to other countries, but it is increasing especially in the group of healthy women with a singleton pregnancy in vertex position at term. One would expect this to coincide with improved outcomes for mothers and children, which is, however, not the case [5]. Although many suggestions considering the reason for this rise have been made, the answer is not yet clear. We hypothesize that incomplete guideline adherence is a possible cause for the current increase in CS rate. In this study we will determine current Dutch care regarding CS using quality indicators. We will use national as well as international guidelines to select the recommendations, resulting in at least a set of internationally accepted indicators. Because we will also report the current CS rates by classification into the internationally accepted Robson Criteria, international comparison of incidences of CS rates in different subgroups will be possible. In that way, specific indicators and incidences of those indicators might be applicable elsewhere. Furthermore, we will focus on factors that influence guideline implementation, and thus optimal care in the barrier and facilitator analysis.

Although earlier reviews claimed that multifaceted strategies (combinations of many different interventions) are often effective, Grimshaw found that a higher number of intervention components was not related to higher effectiveness [23]. It seems plausible that combined interventions are only more effective than single interventions, if these are addressed at the specific barriers to change. This is also the conclusion of Chaillet *et al*.: in the obstetric setting in general and the CS setting in particular, prospective identification of efficient strategies and barriers to change is necessary to achieve a better adaptation of intervention and to improve clinical practice guideline implementation [24].

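### Table 1 as printed assigns no Robson group to single cephalic births around 36 to 37 weeks, because the bounds of groups 1-5 and group 10 do not meet

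*Protocol article*

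**What the plan says.** Table 1 of the protocol article prints the ten-group classification in full. The first group is "Nulliparous, single cephalic, >37 weeks, in spontaneous labour" and the second is "Nulliparous, single cephalic, >37 weeks, induced or CS before labour". Groups 3 and 4 are "Multiparous (excluding previous CS), single cephalic, >37 weeks, in spontaneous labour" and "Multiparous (excluding previous CS), single cephalic, >37 weeks, induced or CS before labour". Group 5, women with a previous CS and a single cephalic pregnancy, has the same >37 weeks bound. Group 10 is "All single cephalic, < 36 weeks, (including previous CS"). Groups 6 to 9 are the breeches, multiple pregnancies and abnormal lies, with no gestational limit.

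Under The assessment of current care, Design and methods, the CS percentages per risk group are to be calculated by this table. Outcome measures in the same part lists the comparison of Dutch practice with international data by the Robson criteria as a secondary outcome. The Discussion relies on it: "international comparison of incidences of CS rates in different subgroups will be possible". Study population and setting excludes only major congenital malformation and fetal death before the onset of delivery, so no birth is excluded for its gestational age.

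**The concern.** A classification used to report CS rates by group should place each woman in exactly one group. Here the two bounds that divide single cephalic births by gestational age are different numbers, and both signs are strict. Births between the bounds can be sampled, since nothing excludes them, yet the table gives them no place and no other section says how to classify them.

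At stake is one secondary outcome. If coders follow the table as printed, groups 1 to 5 lose their earliest births and group 10 loses its latest. The group counts then fall short of the number of women sampled, and the group-specific CS rates describe a narrower range of gestation than data divided at a single cut-point. The gap also reaches into the population that motivates the study, "healthy women with a singleton in vertex position between 37 and 42 weeks gestation". In completed weeks, the whole of week 37 falls outside groups 1 to 5.

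**Working it through.** The article gives no figure to reproduce. The check is whether the printed bounds cover every gestational day of a single cephalic birth.

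**Inputs (all from Table 1).** Groups 1 to 5: >37 weeks. Group 10: <36 weeks. Groups 6 to 9: not single or not cephalic, so not available to these births.

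**Method.** Let d be gestational age in days, so that 36+0 is 36 × 7 = 252 and 37+0 is 37 × 7 = 259. A day is unclassified if it meets neither bound. The table does not say whether weeks are exact time or completed weeks, so both are tried. The same is done for inclusive signs, in case the printed ones lost a bar, and for a single cut-point.

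| Bounds | Unit | Groups 1-5 take | Group 10 takes | Unclassified |
|---|---|---|---|---|
| >37 and <36 (as printed) | exact time | d > 259 | d < 252 | 252 to 259: 36+0 to 37+0, 8 days |
| >37 and <36 (as printed) | completed weeks | d ≥ 266 | d < 252 | 252 to 265: 36+0 to 37+6, 14 days |
| ≥37 and ≤36 | exact time | d ≥ 259 | d ≤ 252 | 253 to 258: 36+1 to 36+6, 6 days |
| ≥37 and ≤36 | completed weeks | d ≥ 259 | d ≤ 258 | none |
| ≥37+0 and <37+0 | days | d ≥ 259 | d < 259 | none |

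The printed bounds leave a gap under either unit. Inclusive signs close it only if weeks means completed weeks. A single complementary cut-point closes it under any reading.

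**Number of women.** This would need the distribution of gestational age among sampled single cephalic births. The article does not give it.

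**The case against.** The strongest objection is that the strict signs may not be what the authors wrote. The neighbouring integers 37 and 36 are what would remain if inclusive signs lost their bars in typesetting or in reading the PDF. With those signs and completed weeks there is no gap. This is a real possibility, and the signs should be checked before anything is changed. It does not dispose of the point: the text at hand has only strict signs, the unit is not stated, and inclusive signs in exact time still leave 6 days without a group.

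A second objection is that the article condenses a cited, internationally used classification, and coders may work from that source. This also stands in part. The article does not say that births at 36 to 37 weeks are left out; their loss follows only from applying the printed table literally. But the methods text names Table 1 as the basis for the percentages, so the table should be right.

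A third objection concerns reach. The data come from a retrospective record search, so if gestational age is recorded women can be regrouped at analysis without new data collection. That is correct and keeps the severity low.

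Three stronger readings are tempting and are not supported:

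- A reader might apply a guessed share of births at these weeks to all 2,000 women. The article gives no such share. The sample is selected on outcome (1,000 CS and 1,000 vaginal births), so a share of all births would not carry over, and the 2,000 include breech, multiple and abnormal-lie births that the gap does not touch.
- A reader might infer that the table contradicts a study definition of term. The abstract and Background describe the women in whom the rise in CS was largest; they do not define term for the study.
- A reader might say that the group percentages no longer sum to the whole. CS percentages within groups never do. Only the group counts should sum to all women.

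**Conclusion.** The point holds as a minor error of definition. Table 1 as printed is not exhaustive for single cephalic births: 8 gestational days (36+0 to 37+0) have no group in exact time, and 14 days (36+0 to 37+6) have none in completed weeks. That the gap exists rests on no assumption beyond the printed signs. That women would be missing from the results assumes the table is applied literally.

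Neither the number of women affected nor the direction of any change in the group CS rates can be derived from the article. The effect is confined to the secondary Robson comparison. Adherence to the quality indicators is computed from indicator-specific denominators. The sample size figures (300, 960 and 1,000) come from a precision calculation with a clustering adjustment. The before-and-after study uses adherence and CS rates that are not described as Robson-group rates. None of these uses the table's bounds.

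**What to change.** First check the signs in Table 1 against the source classification. Then use one complementary cut-point and state the unit: groups 1 to 5 at ≥37+0 weeks and group 10 at <37+0 weeks, in weeks and days. This leaves no day unclassified and agrees with the 37-week lower limit of the population described in the abstract. Add a data check that every single cephalic birth with a recorded gestational age falls in exactly one of groups 1 to 5 and 10, and report the number with gestational age missing.

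The cost is a table correction, one line in the data dictionary and one programmed check. If gestational age is in the records collected, no new data are needed.

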**Group 1: ICU admission**	
-	Admission to ICU or coronary care unit, other than for standard postoperative recovery
**Group 2: Uterine rupture**	
-	Clinical symptoms (pain, fetal distress, acute loss of contractions and haemorrhage) that led to an emergency CS, at which the presumed diagnosis of uterine rupture was confirmed
-	Peripartum hysterectomy or laparotomy for uterine rupture
**Group 3: Eclampsia/ HELLP syndrome**	
-	Eclampsia
-	HELLP syndrome only when accompanied by liver haematoma or rupture
**Group 4: Major obstetric haemorrhage**	
-	Transfusion need of > 4 units of packed cells
-	Embolisation or hysterectomy for major obstetric haemorrhage
**Group 5: Miscellaneous**	
-	Other cases of severe maternal morbidity to the opinion of the treating obstetrician, not to be included in group 1-4

#### Study population and setting

In order to create a representative view of the current obstetrical care in The Netherlands, a multi-centre study will be carried out. Twenty hospitals of different Dutch regions will participate in this study, including university teaching hospitals, non-university teaching hospitals and non-university, non-teaching hospitals. The present study will take place in the setting of a Dutch Obstetric Research Consortium in which all the participating hospitals collaborate.

In the participating hospitals, data on basic obstetrical care and adherence to the quality indicators will be collected. Per hospital 100 women will be selected from the local database: 50 women who delivered by CS and a random set of 50 women who delivered vaginally in the same time period. Exclusion criteria will be a major fetal congenital malformality and fetal death prior to onset of delivery.

#### Outcome measures

The main outcome is adherence to the guideline recommendations, based on the adherence to the quality indicators. Therefore, basic obstetrical data and indicator specific data will be gathered. For example, consider the indicator ‘every woman with a child in breech presentation at 34 to 36 weeks gestation should be offered external cephalic version unless a contraindication for external cephalic version is present.’ This implies that we need to assess the incidence of breech presentation at 34 to 36 weeks gestation, as well as data that show whether an external cephalic version is being offered. Furthermore, we will note in which cases this procedure was not offered for a valid reason. This will allow us to determine the frequencies of adherence for this indicator.

The secondary outcomes are the number of preventable CS, and Dutch practice as compared to international data using the Robson criteria.

#### Sample size considerations

Assuming an adherence to the guidelines of 75%, an alpha of 0.05, and a precision of the estimation of 5%, 300 patients must be included. However, this number has to be adapted to take clustering of data across clinicians and within obstetrical departments into account. Assuming an intra-cluster correlation (ICC) of 0.2 and 80 professionals in 20 hospitals, 960 medical records need to be analysed. In order to compensate for loss to follow-up or incomplete data, 1,000 women with a CS will be included in 20 hospitals within a timescale of three to four months. In order to enable the calculation of specific events, as described in ‘outcome measures,’ a random selection of 1,000 women with a vaginal birth will be included. Thus, there will be 2,000 participants, *i.e.*, 1,000 women after a caesarean delivery and 1,000 women after a vaginal birth. Sampling fraction will be adjusted to the fraction of women with CS in each individual hospital.

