#### Data analysis

The frequencies of adherence per quality indicator will be calculated. This will be calculated by dividing the total number of women who apply for an indicator and for whom care was appropriate by the total number of women who apply for an indicator. For example, women with a child in breech presentation between 34 to 36 weeks of gestation, without contraindication for external cephalic version, should have been offered an external cephalic version. Adherence is the total number of women with a child in breech presentation between 34 to 36 weeks of gestation without contraindication for external cephalic version, in whom an external version was offered, divided by the total number of women with a child in breech presentation between 34 to 36 weeks of gestation without contraindication for external cephalic version.

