#### Study population and setting

The implementation strategy will be executed and evaluated in 12 hospitals (see sample size calculation) that also participated in the current care study: six intervention hospitals in which the newly developed strategy will be applied; and six control hospitals in which care as usual will be offered. In order to select these 12 hospitals, all 20 hospitals of the current care study will be categorized into university, non-university teaching, and non-university non-teaching hospitals (three categories). Within these three categories, possible hospital pairs will be made based on pre-intervention adherence to quality indicators and CS rates, as measured in the current care study. To get a sample representative for the Dutch setting, in total two university hospitals, six non-university teaching hospitals and four non-university, non-teaching hospitals will be asked to participate. Subsequently, the participating hospitals have to be assigned to the intervention and control group. This will be done per stratum and based on geographic region. The evaluation will include an effect, process, and cost analysis. Just as in de current care study, the effects will be measured both at medical outcome level (*i.e.,* CS rates and complication rates) and on guideline adherence level. Satisfaction with and applicability of the tailor-made implementation strategy for both patients and healthcare professionals will be measured in a process evaluation. Information regarding the process will be gathered in a qualitative study in the hospitals in which the implementation strategy was applied. Individual interviews will take place among the involved healthcare professionals and patients to gather data about experiences with the changed care. During the interview, they also will be asked about which elements of the tested strategy they specifically used to implement the evidence-based guidelines; how satisfied they are with the different elements; and their opinion about the feasibility of the different elements.

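### The 5% precision is computed with all caesarean records in the denominator, but adherence is reported per indicator among eligible women only, so it is not secured for indicators that apply to a subgroup

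*Protocol article*

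**What the plan says.** All places are in the Protocol article.

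- **The assessment of current care, Sample size considerations.** The starting point is a single proportion: "Assuming an adherence to the guidelines of 75%, an alpha of 0.05", with "a precision of the estimation of 5%, 300 patients must be included". Clustering is then added: "Assuming an intra-cluster correlation (ICC) of 0.2 and 80 professionals in 20 hospitals, 960 medical records need to be analysed". To allow for incomplete data, "1,000 women with a CS will be included in 20 hospitals". A second group joins the sample without a precision statement; the sentence on it begins "In order to enable the calculation of specific events, as described in ‘outcome measures,’ a random selection of 1,000 women with a vaginal birth will".
- **The assessment of current care, Outcome measures and Data analysis.** The main outcome is guideline adherence as measured through the quality indicators. "The frequencies of adherence per quality indicator will be calculated", and each denominator contains only the women to whom that indicator applies. The worked example is a narrow group: breech presentation at 34 to 36 weeks with no contraindication to external version. No adherence measure combined over indicators is defined.
- **Controlled before-and-after study, Study population and setting.** The results are used again, since "possible hospital pairs will be made based on pre-intervention adherence to quality indicators and CS rates".

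**The concern.** The quantity that was sized is not the quantity that will be reported. The calculation has no term for the share of women eligible for an indicator, so its 5% applies only if an indicator covers practically the whole CS sample. The indicators are to come from three subjects, two of which are planned and emergency CS. Those are separate groups, so among CS women at most one of the two can approach full coverage. The groups named as likely targets (non-progressing labour, previous CS) are also subgroups.

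At stake is how far the indicator results can be trusted. They are used to describe current care and variation between hospitals, to choose target groups with low adherence, and to help form hospital pairs. A reader who carries the 5% over to a subgroup indicator would overrate its precision.

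**Working it through.** **Inputs from the sample size section:** adherence p = 0.75, alpha 0.05 (sidedness not stated; a two-sided 95% interval is taken), precision d = 0.05 (read as the half-width of the interval), ICC 0.2, 80 professionals. **Assumed:** the number of eligible women n, since the document gives no eligible fractions, and an even spread of those women over the 80 professionals.

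**Step 1: reproduce the plan's figures.** The formula is z² p(1 − p)/d².
- With z = 2: 4 × 0.1875/0.0025 = 300, the stated figure.
- With z = 1.96: 288.1.
- Records per professional: 960/80 = 12. Design effect: 1 + (12 − 1) × 0.2 = 3.2. Then 300 × 3.2 = 960.

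Both figures reproduce, and 960 does so only with all 960 records in the denominator.

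**Step 2: eligible women needed for 5 points.** With n eligible women the design effect is 1 + (n/80 − 1) × 0.2 = 0.8 + 0.0025n. Setting n/(0.8 + 0.0025n) = 288.1 gives n = 0.8 × 288.1/(1 − 0.0025 × 288.1) ≈ 824. That is 824/1,000 = 82% of the CS women, or 824/2,000 = 41% of all women. The latter is unweighted; weighting back from the equal CS and vaginal samples could reduce the gain. With the protocol's rounded 300 in place of 288.1, the answer is 960.

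**Step 3: half-width by eligible number.** Half-width = 1.96 × √(p(1 − p) × DE/n), with DE = max(1, 0.8 + 0.0025n). The 50% and 90% columns show the dependence on adherence.

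| Eligible n | Share of 960 | DE | p = 0.75 | p = 0.90 | p = 0.50 |
|---|---|---|---|---|---|
| 960 | 100% | 3.20 | 4.9 | 3.4 | 5.7 |
| 824 | 86% | 2.86 | 5.0 | 3.5 | 5.8 |
| 480 | 50% | 2.00 | 5.5 | 3.8 | 6.3 |
| 240 | 25% | 1.40 | 6.5 | 4.5 | 7.5 |
| 96 | 10% | 1.04 | 8.8 | 6.1 | 10.2 |
| 50 | 5% | 1.00 | 12.0 | 8.3 | 13.9 |

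Half-widths are in percentage points. The design effect shrinks with the clusters, so the loss is modest for broad indicators and large for narrow ones.

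**Step 4: break-even at other adherence levels.** Repeating step 2 gives about 510 eligible women at 80% adherence and 169 at 90%. At 60% it gives about 3,780, more than the 2,000 women in the study.

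**Step 5: single hospitals.** Each hospital contributes 100 women. If 5, 10 or 20 of them are eligible (assumed), the standard error at 75% is √(0.1875/5) = 19.4, √(0.1875/10) = 13.7 or √(0.1875/20) = 9.7 points. Clustering within the hospital is ignored here.

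**The case against.** The strongest reply is that the protocol never promises 5% for each indicator. It speaks of adherence to the guidelines as a whole, and its arithmetic is sound. Both points are correct: this is a mismatch of denominators, not a calculation error. But the estimate to which the 5% would belong is not defined in the analysis. The article states both the calculation and the estimator, so this is not a detail left to a fuller document.

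A second reply is that the consequences are contained. Target groups must combine low adherence with high incidence, which works against very narrow indicators. The sample size of the controlled study is to be calculated afresh from the observed data. The current-care analysis is descriptive, and the vaginal births can enlarge some denominators. All of this stands and limits the damage. It does not remove it: low adherence is what is being sought, and step 4 shows that the number needed rises steeply below 75%. No precision is given for the enlarged denominators.

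A reader might also infer that most indicators will miss 5%. The document does not support that. The indicators do not exist yet, neither their eligible fractions nor their adherence is known, and one with 90% adherence would need only about 169 eligible women.

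Nor does the text say that hospitals are paired on raw percentages for single indicators. It groups hospitals by type first, then pairs on adherence together with CS rates, and the controlled study is analysed with a multilevel model. The small per-hospital denominators call for caution; they do not show that the pairing is flawed.

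**Conclusion.** The concern holds in limited form. The sample size secures a 5-point half-width only for an estimate that uses nearly all CS records, whereas the main outcome is reported per indicator among eligible women. At 75% adherence, ICC 0.2 and 80 professionals the threshold is about 824 eligible women. Below it the loss is small for an indicator covering half of the 960 records and substantial for one covering a tenth or less. These sizes rest on assumed eligible numbers, an even spread over professionals and unweighted counts. How many indicators are affected cannot be determined from the document.

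**What to change.** In the current-care sample size section, state that the 5% holds only for indicators with about 824 or more eligible women at 75% adherence. Replace the single figure with a short table of expected half-width by number of eligible women and adherence level, such as the one above, marked as illustrative until the indicators are fixed. Optionally, add a caution that per-hospital indicator percentages rest on small denominators where they are used for pairing or for describing variation between hospitals.

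The cost is a few lines of text and no additional records. The drawback is that the stated precision becomes less favourable for indicators that apply to a subgroup.
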